Health utilisation and cost data will be collected from the rehabilitation facilities (inpatient care), outpatient services, and via a patient health service utilisation questionnaire administered at 6 months and 12 months post intervention. The questionnaire will include questions on health service utilisation including allied health and medical services, pharmaceutical use, and hospital admissions. In addition, Medicare Australia claims records will be retrieved with patient permission for 12 months post discharge to determine health service use post discharge including allied health, medical services, pharmaceutical use and hospital admissions. The amount of physiotherapy and occupational therapy intervention (number of treatment sessions, discharge planning, equipment hire or purchase, team meetings, staff discussions and family meetings) received by each group will be recorded via each hospital's allied health access database program, including the additional Saturday interventions received by the intervention group and any missed sessions as a result of medical instability, patient refusal and a patient not being ready to attend treatment on time.

The use of these tools will enable us to complete a cost utility analysis examining the cost per quality adjusted life-year saved and cost per 10% change in functional independence. We will assess health related quality of life and functional status at both 6 months and 12 months to try and minimise loss-to-follow-up as an intention-to-treat analysis will be undertaken.

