## Data analysis

### Sample size estimation

Sample size estimation is based on rehabilitation length of stay data [28]. For length of stay, with a maintained effect size of .21 and power of 0.80 a sample size of 356 participants in each group is required (total of 712 participants).

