### Statistical analysis

Between group differences of the primary outcomes (length of stay, EuroQol, and FIM) will be analysed with analysis of covariance of discharge scores with the baselines score as covariate [45]. Intention to treat analysis will be used with any missing health outcome data imputed using the last value carry forward method [46].

A rigorous economic evaluation will be carried out alongside the randomised clinical trial. Cost effectiveness of the intervention will be determined as the incremental cost of additional Saturday allied health inpatient rehabilitation services compared to usual inpatient rehabilitation per quality adjusted life year saved. The primary measure of incremental effect for the economic evaluation will include the difference in health related quality of life between the control and treatment groups using the EuroQol. A secondary incremental cost effectiveness ratio will be determined using the cost per change in functional status using the FIM.

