Patient level costing and utilisation data for inpatient rehabilitation services from the hospital's costing and admission and discharge system will be used to estimate the costs of inpatient care. Following discharge, the patient health service utilisation questionnaire will be administered at 6 and 12 months to determine the health care services used post discharge. Costs will be attributed to these services based on published costing data from the National Hospital Cost Data Collection, Medicare Australia, and the Pharmaceutical Benefits Scheme. Where a patient is re-admitted to one of the participating rehabilitation facilities within the 12-month period inpatient costing data will be used. Medicare Australia data will be used to obtain private health service utilisation. The costs of implementing the intervention (Monday to Saturday rehabilitation) and the control programs (Monday to Friday rehabilitation) will be determined from the rehabilitation facility. This will include therapist time, equipment, consumables and administrative overheads. The incremental cost estimate will be determined as the difference in cost of implementing the Saturday allied health rehabilitation service plus the difference in health service costs (including out-of-pocket private expenditure) used in the 12 months post discharge between the control and intervention groups. A secondary incremental cost estimated will be calculated as the change in resource use resulting from the additional Saturday allied health rehabilitation service compared to usual Monday to Friday rehabilitation at the point of discharge from the inpatient rehabilitation facility. Any missing health service utilisation or cost data, where service use was recorded but a quantity not specified, will be imputed using within group mean cost [47].

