The primary health economic analysis is a cost utility analysis from a health care system perspective, with outcomes based on health related quality of life (using EuroQol), and cost effectiveness using an intermediate clinical outcome (based on the FIM). We will be undertaking an intention to treat analysis where the cost utility ratio will be calculated as the change in total program and health service cost per change in quality adjusted life year saved in the intervention and control groups at 6 and 12 months. Additional cost effectiveness ratios will be calculated as the total program cost per 10% change in functional independence (at discharge), and the total program and health service cost per 10% change in functional status between the control and intervention groups over a 12 month period. One way sensitivity analysis will be undertaken to investigate the robustness of the cost effectiveness ratio to a range of cost and effect estimates, including alternative delivery arrangements, wage rates and program length on the cost side, and health related quality of life and FIM on the effect side.

Between group differences of secondary outcomes measured on continuous or ordinal scales will be analysed with analysis of covariance of discharge scores with the baselines score as covariate [45]. Between-group differences in discharge destination (home versus other) will be analysed with relative risk ratios.

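### Missing cost quantities are filled with the arm mean, which overstates the precision of costs, and this rule has a narrower scope than the carry-forward rule for health outcomes

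*Protocol article*

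**What the plan says.** Three statements in the Statistical analysis section of the Protocol article bear on this point.

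- Costs: missing utilisation or cost data, "where service use was recorded but a quantity not specified, will be imputed using within group mean cost".
- Health outcomes: "any missing health outcome data imputed using the last value carry forward method". This rule has no restriction of scope.
- Population for the economic analysis: "We will be undertaking an intention to treat analysis where the cost utility ratio will be calculated" at 6 and 12 months.

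Costs come from several sources. Inpatient costs use "Patient level costing and utilisation data for inpatient rehabilitation services from the hospital's costing and admission and discharge system". After discharge, "the patient health service utilisation questionnaire will be administered at 6 and 12 months to determine the health care services used post discharge". The Primary outcomes measures section adds that "Medicare Australia claims records will be retrieved with patient permission for 12 months post discharge". Programme costs come from the facilities.

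On uncertainty, the article says: "One way sensitivity analysis will be undertaken to investigate the robustness of the cost effectiveness ratio". The examples it lists are delivery arrangements, wage rates, programme length, quality of life and FIM. Missing data is not among them.

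**The concern.** The rule for missing quantities is stated outright, so this is an objection to a choice and not to a gap. Putting the arm's mean in place of an unknown quantity adds values that do not vary and then counts them as data. It also sets aside patient information that the trial collects and that could predict service use: case-mix, site, comorbidity, function and length of stay.

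The cost rule and the outcome rule also differ in scope. The cost rule works only if some use was recorded. The outcome rule fills whatever is missing. A patient who misses a 6- or 12-month contact has EuroQol filled under one rule, while the other has nothing to say about that patient's questionnaire costs.

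Health utilisation and cost data are named among the primary outcomes in the Abstract, and the primary aim in the Background is framed around reducing the cost of care. An overstated precision for cost, or a cost total with an unequal gap in it, would affect the main economic conclusion. None of the sensitivity analyses listed would reveal either.

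**Working it through.** **The plan's own figure.** The only design figure that can be checked is the sample size: "with a maintained effect size of .21 and power of 0.80 a sample size of 356 participants in each group is required". With a two-sided 5% level (assumed; the article does not state it), n = 2(1.960 + 0.842)²/0.21² ≈ 356 per group, which agrees. It concerns length of stay and is not in dispute.

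**Inputs.** The imputation rules and cost sources are those of the article. It gives no missing rate and no breakdown of cost variance, so two quantities are assumed and varied:
- m, the share of patients with recorded use of an item whose quantity is missing, taken as equal in the arms and missing completely at random;
- w, the share of total-cost variance due to variation in that item, taken as independent of the rest.

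The filled mean is taken to be the mean over patients in the arm with recorded use and a known quantity.

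**Effect on the estimate.** With n values in an arm and observed mean x̄, the filled mean is [n(1-m)x̄ + nm·x̄]/n = x̄. The arm means, and so their difference, are unchanged by the filling.

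**Effect on precision, the item itself.** Naive variance of the mean ≈ (1-m)S²/n. Correct variance = S²/[(1-m)n]. Ratio of standard errors, naive to correct = 1-m. True coverage of a nominal 95% interval = 2Φ(1.96 × ratio) - 1.

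**Effect on precision, total cost.** Ratio = √{[w(1-m) + (1-w)] / [w/(1-m) + (1-w)]}. For w = 10% and m = 10%: √(0.990/1.0111) = 0.990. For w = 50% and m = 30%: √(0.850/1.2143) = 0.837.

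Standard-error ratio and true coverage:

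| w | m = 5% | m = 10% | m = 20% | m = 30% |
|---|---|---|---|---|
| 100% (the item itself) | 0.95; 93.7% | 0.90; 92.2% | 0.80; 88.3% | 0.70; 83.0% |
| 50% | 0.975; 94.4% | 0.949; 93.7% | 0.894; 92.0% | 0.837; 89.9% |
| 10% | 0.995; 94.9% | 0.990; 94.8% | 0.978; 94.5% | 0.964; 94.1% |

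**Scope of the two rules for a patient with no 6- or 12-month questionnaire.**
- EuroQol and FIM: filled by carry-forward.
- Inpatient and programme costs: available from hospital and facility records.
- Medicare claims: available if the patient gave permission.
- Costs known only from the questionnaire: no use recorded, so the stated rule does not apply.

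If 10%, 20% or 30% of patients had no questionnaire (assumed), that would be 0.10, 0.20 or 0.30 × 712 ≈ 71, 142 or 214 patients.

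**The case against.** The strongest reply has four parts.

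1. The article specifies no confidence interval or test for cost. The analysis of covariance names length of stay, EuroQol and FIM, and the cost-effectiveness ratio is to be examined by one-way sensitivity analysis. This stands: the loss of precision is conditional on someone computing an interval or test from the filled data.

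2. The rule is narrow. It touches only recorded use without a quantity, while hospital, programme and claims costs lie outside it. This also stands, and it is why the top row of the table must not be read as the effect on total cost.

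3. A reader might infer that filling from the patient's own arm reinforces the arm difference. It does not, as the algebra shows. Bias needs quantities to be missing in a way related to their size, and nothing in the article says that they are.

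4. A reader might also infer that patients without a questionnaire have no cost at all, that costs and outcomes would therefore rest on different patients, and that the intention-to-treat claim fails. The article does not support this. Such patients keep hospital and programme costs and, with permission, claims covering allied health, medical services, pharmaceuticals and admissions. The article does not say that they are dropped or set to zero. A rule for wholly missing questionnaires may also sit in a fuller document, so its absence here is not a fault.

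What remains is the method chosen for item gaps, and the difference in scope between two rules that feed the same ratio.

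**Conclusion.** The point holds in a limited form. Within-group mean imputation is a poor choice for a named primary outcome because any standard error, interval or test on the filled costs will be too narrow. The factor is 1-m for the item. For total cost it is nearer to 1: about 0.99 with w = 10% and m = 10%, and 0.84 with w = 50% and m = 30%. These figures rest on assumed m and w, on quantities missing completely at random, and on independence between the item and other costs. The documents cannot say where in that range the trial will fall.

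The scope mismatch is real on the page, but its consequence is only possible: the questionnaire-based part of cost could be incomplete for patients whose EuroQol is filled. It does not show that the intention-to-treat analysis fails. The sample size is unaffected.

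**What to change.** Replace within-group mean imputation with multiple imputation, run within each arm and jointly for the cost components and EuroQol, on all randomised patients. It should cover both missing quantities and wholly missing questionnaires. Predictors: case-mix, site, age, Charlson index, baseline and discharge FIM and EuroQol, length of stay, and Medicare claims where available. Pool the results across imputations so that any standard error or interval reflects the missing data, and add the missing-data assumption to the listed sensitivity analyses.

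The cost is a change of wording in the analysis plan and modest extra programming. No new data collection and no change to the sample size are needed. Two things need care: costs are likely to be skewed, so the imputation model must allow for that, and Medicare claims depend on patient permission and will themselves be incomplete for some patients.

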### Participants

Participants will be included if they are:

• aged 18 years or older

• have been admitted for rehabilitation at either of the two rehabilitation facilities.

Participants will be excluded if they

• do not give informed consent to participate in the trial, or

• if they are admitted for geriatric evaluation and management, as this patient group are managed differently to patients admitted for rehabilitation, or

• if they are already enrolled in another intervention trial.

Participants will not be excluded if their primary language is a language other than English. A language interpreter will be provided to ensure these patients understand the informed consent procedure and to assist them with the administration of the quality of life and clinical outcome measures. Participants will not be excluded if assessment indicates reduced cognition, as indicated by a score of less than 24/30 on the Mini-mental State Examination [30] since cognitive impairment is common in patients receiving rehabilitation [31]. Our pilot data found that 24% of patients admitted for rehabilitation had severe cognitive impairment [28]. Written informed consent will be sought from all eligible patients admitted for rehabilitation. For patients with impaired cognition or aphasia, the next of kin will be approached for informed consent.

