### Secondary outcome measures

Secondary outcomes measures include the 10 metre walk test [40], the timed up and go test [41], and the Personal Care Participation Assessment and Resource Tool (PC-PART) [42]. The modified motor assessment scale [43] will be completed on patients with a neurological diagnosis. All secondary outcome measures are designed to evaluate clinical outcomes relevant to the functional goals of therapy, and will be measured on admission and at discharge.

Discharge destination will be recorded as home, high level residential care, low level residential care, and acute hospital transfer. This will be recorded as "worse" when the participant was discharged to a destination where more assistance would be provided, for example a high level residential care facility, or "same" when a participant was discharged to the same place of accommodation prior to the hospital admission. This outcome measure is included to measure any increase in burden of care to the community.

Demographic data on participant age, gender and co-morbidities will be documented from each participant's medical chart. Co-morbidities will be recorded using the Charlson co-morbidity index [44].

Adverse events, including falls, nosocomial infections and mortality will be recorded on an incident report form through an audit of participants at discharge and the rehabilitation facilities' incident reporting database. Follow-up physiotherapy and occupational therapy will be recorded at discharge as outpatient, community rehabilitation (including centre-based and home services), or no follow up.

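### Discharge destination is defined relative to prior accommodation but analysed as home versus other, which misclassifies prior care-facility residents and loses precision

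*Protocol article*

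**What the plan says.** In the protocol article, Secondary outcome measures sets up this outcome in three steps.

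- Raw categories: "Discharge destination will be recorded as home, high level residential care, low level residential care, and acute hospital transfer". Home is a separate category from both levels of residential care.
- Coding: the outcome is *worse* if the destination gives more assistance, and *same* "when a participant was discharged to the same place of accommodation prior to the hospital admission". This coding needs prior accommodation to be known.
- Purpose: "This outcome measure is included to measure any increase in burden of care to the community".

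Statistical analysis then gives one rule for the outcome: "Between-group differences in discharge destination (home versus other) will be analysed with relative risk ratios". It does not refer to prior accommodation or to the *worse*/*same* coding, and it does not say whether home or other is the event.

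Under Participants, adults qualify if they "have been admitted for rehabilitation at either of the two rehabilitation facilities". None of the listed exclusions concerns living in residential care before admission.

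**The concern.** The outcome is defined as a change from the participant's own starting point, but the analysed variable is an end state that ignores the starting point. The two agree only if everyone starts from home, and the eligibility criteria do not ensure that.

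The Discussion presents the trial as testing whether stay can be shortened without compromising discharge outcomes, and discharge destination is one of the measures a reader will consult for that. A finding of no difference will be taken as reassurance. If some participants are classed by where they already lived, the comparison is less able to show a real increase in burden. Meanwhile the coding designed for this purpose is recorded but has no stated analysis.

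**Working it through.** **The plan's own figure.** The only design figure is the sample size, which rests on length of stay. Sample size estimation reads: "with a maintained effect size of .21 and power of 0.80 a sample size of 356 participants in each group is required". Taking two-sided alpha 0.05 (assumed, as it is not stated), n = 2 × (1.960 + 0.842)² / 0.21² = 15.70 / 0.0441 = 356 per group, which matches. The point does not affect this figure; 356 serves below only as the arm size. The article gives no design figure for discharge destination.

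**The two codings side by side.**

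| Before admission → discharge | Definition (Secondary outcome measures) | Analysis (Statistical analysis) |
|---|---|---|
| Home → same home | same | home |
| Home → residential care | worse | other |
| Residential care → same facility | same | other |
| Low-level → high-level care | worse | other |

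The codings disagree in the third row. Because the third and fourth rows both become *other*, the analysis cannot separate a resident who went back from one who now needs more care.

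**Illustration of size.** The article gives no destination rates and no share of prior residents, so every input here is assumed:

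- 10% (control) and 15% (intervention) of people admitted from home go to a worse destination;
- a share r of each arm came from residential care, and all of them return to the same facility.

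The relative risk of *worse* is [(1 − r) × 0.15] / [(1 − r) × 0.10] = 1.50 at every r.

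The relative risk of *other* is [r + (1 − r) × 0.15] / [r + (1 − r) × 0.10]:

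| r | *Other*, control | *Other*, intervention | Relative risk |
|---|---|---|---|
| 0% | 0.100 | 0.150 | 1.50 |
| 2% | 0.118 | 0.167 | 1.42 |
| 5% | 0.145 | 0.193 | 1.33 |
| 10% | 0.190 | 0.235 | 1.24 |
| 15% | 0.235 | 0.277 | 1.18 |

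The relative risk of *home* is [(1 − r) × 0.85] / [(1 − r) × 0.90] = 0.944 at every r, so with home as the event there is no dilution.

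**Precision at r = 10%, 356 per arm.** The risk difference is 0.9 × 0.05 = 0.045 under either coding. Its standard error is √{[p₁(1 − p₁) + p₂(1 − p₂)] / 356}:

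- *worse* (0.090 v 0.135): √[(0.0819 + 0.1168) / 356] = 0.024;
- home versus other (0.190 v 0.235): √[(0.1539 + 0.1798) / 356] = 0.031.

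The second is about 30% larger. Power for this difference is about 48% on *worse* and 31% on home versus other.

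**The case against.** The strongest reply is that the analysis section gives one clear instruction. Home versus other follows directly from the four recorded categories, and every participant falls on one side of it. The *worse*/*same* pair is not exhaustive: someone discharged to less assistance than before admission fits neither. This is also a secondary outcome, and the question of harm is addressed as well by the FIM and EuroQol to 12 months and by post-discharge service use. All of this stands. It limits the weight of the point and shapes the fix, but it does not explain why the coding tied to the stated purpose has no analysis.

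Three stronger readings are tempting, and the article does not support them.

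- *The analysis no longer measures burden of care.* For participants admitted from home, leaving for anywhere other than home still tracks a move to more assistance. Only prior residents are misclassified, and their share is unknown. If it is near zero, the codings nearly coincide.
- *The relative risk is always pulled towards 1.* That holds only if *other* is the event. The article does not name the event, and with home as the event the ratio stays at 0.944 in the illustration.
- *The comparison is biased towards one arm.* Randomisation should balance prior residents between arms. What remains is misclassification and noise.

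A particular regression model or a rule for deaths would go beyond this defect. Those are details that a full protocol or analysis plan would normally settle.

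**Conclusion.** The point holds. The definition and the analysis of discharge destination do not match, and this can be read from the text without any calculation. As written, the analysis classes a resident who returns to the same facility with people whose need for care has risen, and it hides a move from low-level to high-level care.

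The consequence is misclassification against the stated purpose and lost precision. Its size cannot be established from the article. On the assumed rates, with *other* as the event, the relative risk falls from 1.50 to between 1.42 and 1.18 as prior residents rise from 2% to 15% of the sample. Whichever side is the event, the standard error of the risk difference is about 30% larger at a 10% share. Length of stay, the other primary outcomes and the sample size are unaffected. The correction is worth making because it is specific and nearly free.

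**What to change.** In Statistical analysis, make *worse* versus not worse the analysed outcome, where not worse means the same or less assistance than before admission, so that every discharge is classed. Name *worse* as the event and report the relative risk with a 95% confidence interval. State how acute hospital transfer is classed. Keep home versus other as a descriptive summary.

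The cost is a sentence or two of text and one extra descriptive table. No new data are needed, because the *worse*/*same* coding and the raw destinations are already to be recorded. The change is best made before any results by group are seen, so that the coding cannot be chosen in light of them.

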### Randomisation

Participants will be randomised to the additional allied health services (intervention) group or the control group with a concealed method, using permuted blocks of 4, 6 and 8, stratified for case-mix status (neurological and other/orthopaedic) and site (two sites). Stratification will include site in order to facilitate the staffing of the Saturday service. The block allocation sequence will be generated by http://www.randomization.com and assignments sealed in sequentially numbered opaque envelopes. Only after the participant has enrolled in the trial and completed written informed consent and baseline testing will assignment be made by the project officer by opening the next envelope in the sequence. A member of the research team who is not involved in participant recruitment, assessment or treatment will be responsible for preparing the envelopes.

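### The analyses name neither randomisation stratum; if case-mix or site predicts discharge destination, an unadjusted relative risk is valid but conservative, an avoidable weakness in a check on added burden of care.

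*Protocol article*

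**What the plan says.** Under Randomisation, the protocol article allocates participants "using permuted blocks of 4, 6 and 8, stratified for case-mix status (neurological and other/orthopaedic) and site (two sites", which makes four strata. It gives a reason for one of the two factors: "Stratification will include site in order to facilitate the staffing of the Saturday service".

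Under Secondary outcome measures, it explains why discharge destination is recorded: "This outcome measure is included to measure any increase in burden of care to the community".

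Under Statistical analysis, destination receives one sentence: "Between-group differences in discharge destination (home versus other) will be analysed with relative risk ratios". No stratum, covariate, test or standard error is named. The sentence before it, which covers the other secondary outcomes and names only the baseline measure as covariate, begins: "Between group differences of secondary outcomes measured on continuous or ordinal scales will be analysed with analysis of covariance of discharge scores with the baselines". The primary outcomes are treated in the same way. Neither case-mix nor site appears in any analysis that the article describes.

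**The concern.** Blocked allocation within strata makes the arms nearly identical in case-mix and site. The usual standard error of an unadjusted relative risk still allows for chance imbalance on those factors. If the chance of going home differs between strata, that standard error is larger than the true variability of the estimate. The interval is then too wide and the test falls below its nominal level.

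For an efficacy test such conservatism is usually harmless. Here it works in the unhelpful direction. The Discussion frames success as a shorter stay without worse discharge outcomes. In the Background, the pilot's non-significant result for discharge destination is among the findings offered as evidence that quality of care did not suffer. Where a non-significant result is read as reassurance, a blunter test favours the reassuring answer.

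**Working it through.** **1. The plan's own figure.** The article states: "with a maintained effect size of .21 and power of 0.80 a sample size of 356 participants in each group is required (total of 712". Assuming two-sided 5%, n per group = 2(1.96 + 0.8416)² / 0.21² = 15.70 / 0.0441 = 356. The figure reproduces. It concerns length of stay; no size, power or event rate is given for discharge destination.

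**2. Formulas.** Let n = 356 per arm, w_s the share of patients in stratum s, p_as the non-home rate in arm a and stratum s, and P_a = Σ w_s p_as.

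- Unadjusted variance of the log relative risk: Σ_a (1 − P_a)/(n P_a).
- Variance under 1:1 allocation within strata, with a common relative risk: Σ_a [Σ_s w_s p_as(1 − p_as)]/(n P_a²).

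The second is never larger than the first. The two are equal only when the strata have the same rate.

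**3. One case in full** (assumed shares 15/15/35/35%, control non-home rates 42/38/14/10%, relative risk 1.3).

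- P_0 = 0.2040 and P_1 = 0.2652.
- Unadjusted: 0.7960/(356 × 0.2040) + 0.7348/(356 × 0.2652) = 0.01096 + 0.00778 = 0.01874, so SE = 0.1369.
- Stratified: the within-stratum sums are 0.1455 and 0.1664. 0.1455/(356 × 0.2040²) + 0.1664/(356 × 0.2652²) = 0.00982 + 0.00665 = 0.01647, so SE = 0.1283.
- Ratio: 0.1369/0.1283 = 1.067.
- Power with ln 1.3 = 0.2624. Unadjusted: Φ((0.2624 − 1.96 × 0.1369)/0.1283) = 48%. Stratified: Φ(0.2624/0.1283 − 1.96) = 53%.

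**4. Range of assumptions.** All shares and rates below are assumed. The SE excess comes from the formulas, over true relative risks of 1.0 to 1.5. Power (at relative risk 1.3) and type I error come from simulations of 712 patients with 20,000 or 40,000 trials per setting. They compare the unadjusted ratio with a Mantel-Haenszel ratio using the Greenland-Robins variance; each pair is unadjusted v stratified.

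| Stratum shares, % | Non-home rates, % | SE excess | Power, % | Type I error |
|---|---|---|---|---|
| 15/15/35/35 | 20/20/20/20 | 0% | 47.3 v 47.3 | 0.048 v 0.048 |
| 15/15/35/35 | 27/23/19/15 | 0.6-0.7% | 46.2 v 46.9 | 0.047 v 0.049 |
| 15/15/35/35 | 32/28/17/13 | 1.7-2.1% | 45.9 v 47.6 | 0.046 v 0.050 |
| 20/20/30/30 | 35/30/12/8 | 4.4-5.6% | 45 v 49 | 0.039 v 0.048 |
| 15/15/35/35 | 42/38/14/10 | 5.6-7.3% | 47.5 v 53.2 | 0.036 v 0.047 |
| 20/20/30/30 | 50/40/10/5 | 12-16% | 54 v 66 | 0.027 v 0.047 |
| 25/25/25/25 | 55/45/12/8 | 12-16% | 73.9 v 82.5 | 0.029 v 0.049 |

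In every row the unadjusted type I error is at or below 5%. Its simulated coverage in the five settings other than the two 20/20/30/30 rows is 95.2% to 97.8%.

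**5. Not calculated.** No figure was derived for the ANCOVAs. The baseline score may already absorb much of the case-mix difference there.

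**The case against.** The strongest reply is that the article never says crude or unadjusted. A Mantel-Haenszel estimate is also a relative risk, and an article may leave such detail to a full protocol or analysis plan that is not shown. This stands as far as it goes: the unadjusted reading is an inference. It is the natural one, because the neighbouring sentences name their covariate and this one names none. For the ANCOVAs less inference is needed: the stated covariate is the baseline score and nothing else.

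A second reply is that the loss depends on the strata predicting destination. The article gives no rates, and its only stated reason for stratifying by site is staffing. This also stands, and the conclusion must be conditional. No operational reason is given for case-mix, however, and neurological patients are treated as distinct enough to have their own motor scale. A difference in home discharge by case-mix is therefore plausible, though not shown.

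A third reply is that destination is a secondary outcome. The no-harm part of the primary aim rests on quality of life and function, and in all but one of the assumed settings with about 20% going elsewhere than home, a relative risk of 1.3 would be missed about half the time either way. That is fair and limits the weight of the point. It is no reason to leave out factors already used to randomise.

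**Conclusion.** The point holds as a conditional matter of efficiency. Case-mix and site shape the allocation but appear in no stated analysis. If either predicts non-home discharge, an unadjusted relative risk is valid but conservative. The loss is negligible for no to moderate stratum differences (standard error 0-2% too large, at most about 2 power points), modest for strong ones (4-7%, 4-6 points) and appreciable for very strong ones (12-16%, 9-12 points). These figures assume 712 patients, a common relative risk of 1.3 for the power losses, and invented stratum rates.

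A reader might infer more: that the plan prescribes a crude analysis, that its interval is certainly too wide, or that the comparison is biased. The documents support none of these. The wording does not exclude a stratified ratio, no rates are given from which excess width could be established, and randomisation keeps the unadjusted comparison valid with type I error at or below nominal.

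**What to change.** In Statistical analysis, state that discharge destination is compared by a relative risk stratified by case-mix and site, reported with its 95% interval. Either a Mantel-Haenszel estimate or a Poisson regression with robust standard errors containing both factors would serve. Enter the same two factors beside the baseline score in the FIM, EuroQol and secondary-score ANCOVAs.

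The cost is about two sentences. Both factors are known for every randomised patient, so no further data or participants are needed, and with no stratum difference essentially nothing is lost.

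While that sentence is being edited, its split into home and other should be reconciled with the worse/same coding under Secondary outcome measures. A resident returning to the same care home is unchanged under one and counts as other under the other. That is a separate matter and does not alter the calculation above.
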